**STATISTICAL METHODOLOGY**

**Sample Size**

Targeted enrollment is 100 adult SICU patients. This study will not be powered to show a difference in the efficacy of preemptive management versus standard care due to single center population constraints in addition to cost limitations. Sample size calculations were therefore based on the number of adult patients expected to be admitted to the SICU over a 1 year period who are likely to meet inclusion criteria (n=700). Based on prior experience, it is reasonable to expect an accrual of 100 patients in a year. Using a 3:1 randomization strategy, 75 will be assigned to active surveillance and 25 to standard care. We estimate that 25% of patients will develop a positive test(13;25;27) and 19 will receive anidulafungin. These numbers should provide sufficient data for a preliminary feasibility evaluation of the preemptive strategy.

**Statistical Analyses**

Statistical analysis will be performed using SAS software. P values and 95% confidence intervals will be 2-tailed and statistical significance set at the 5% level unless otherwise specified.

*Demographics and Baseline Characteristics*

Demographic and baseline characteristic information will be summarized and compared using the Chi-squared test for discrete variables and one way ANOVA for continuous various to assess any imbalance between treatment groups.

*β-D-glucan Test Characteristics*

β-D-glucan test characteristics, using data collected from standard care group, will be described using sensitivity, specificity, positive and negative predictive values. Proven and probable cases of IFI, as defined by EORTC/MSG criteria (**tables 3 and 4**), will constitute the standard for comparison.

*Feasibility Analysis*

Feasibility will be a description of preemptive protocol adherence, BDG test requests off schedule, and the number of patients withdrawn from the preemptive arm due to the initiation of empiric systemic antifungal therapy in the absence of a positive BDG test.

*Efficacy End-Points*

Development of IFI during the study period will be assessed by the principal investigator (PI) and a second blinded investigator using predefined EORTC/MSG criteria for proven or probable disease. The study period is defined as the time the patient was cared for in the SICU. The proportions of patients developing IFI, and IC specifically, in each group will be compared using Fisher’s exact test. The median ICU stay and number of febrile days while in the ICU will be compared using the Kruskal-Wallis test. Patient mortality, overall and attributed to IFI, will also be summarized by group. Response-to-therapy (RTT) will be determined by the PI and a blinded second investigator. The RTT population will consist of all patients who were underwent BDG monitoring for at least 3 days and received at least 1 dose of systemic antifungal therapy.

*RNA Analyses*

Initial signature development cohort: RNA from patients with blood cultures growing *Candida* and an equal number of patients with negative blood cultures and negative BDG testing (controls) will be chosen for signature development. A decision tree approach used previously by our group will be used to find gene expression patterns that are correlated with candidemia to determine the predictive capability of those gene patterns as a diagnostic test(28;29). Once we identify a large number (100-300) of gene expression patterns that significantly correlate with the illness classification in our initial cohort, we will then identify the best combination of 3-5 patterns for discriminating between those with candidemia and those with no infection. Once the best expression patterns are identified, we will perform cross validation analysis in which we construct a decision tree with the best gene patterns using all of the samples except for one “held out” sample. We can then use the decision tree model to predict the classification of the “held out” sample as an honest test of the accuracy of our predictive model and to guard against over-fitting. We plan to define host gene expression patterns in response to candidemia using an initial cohort of up to 30 persons with candidemia and up to 30 persons with no infection. This sample size has 90% power to detect at least a 2-fold change in expression levels in the 70% least variable genes with an alpha of 0.001(30). After establishing robust gene expression signatures that classify individuals as having a “candidemia” or “no infection” we will test the generalizability of these profiles on the remaining patients presenting to the intensive care unit at risk for invasive candidiasis. We will not know beforehand the etiology of their symptoms.

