**Hypotheses:**

**1)** Biweekly β-D-glucan surveillance will identify SICU patients with an invasive fungal infection (IFI) before clinical signs or symptoms develop.

1. Anidulafungin initiated in response to a positive β-D-glucan test (i.e. preemptive therapy) will be well tolerated, safe, and effectively treat patients early, before advanced infection is established.
2. Peripheral blood gene expression signatures obtained serially from at-risk patients can predict early IC.

**Study Design:** Single center, randomized, non-blinded, parallel group, comparative study.

**Sample Size:** 100 subjects; 75 in the active surveillance/preemptive therapy arm and 25 in the usual care arm.

**Study Population:** Adult patients admitted to Duke University Medical Center SICU at-risk for the development of IC.

**Study Drug:** Intravenous anidulafungin initiated in response to a positive β-D-glucan test for subjects in the active surveillance/preemtpive arm. Preemptive treatment will continue for at least 14 days or until ICU discharge (maximum 28 days), which ever is longer.

**Efficacy:** IFI assessments will be made weekly and at SICU discharge.

**Safety:** A data safety monitoring board will review adverse events every 4 months.

**Statistics:** β-D-glucan test characteristics will be described using sensitivity, specificity, positive and negative predictive values. The proportions of patients developing proven or probable IC in each group will be compared using Fisher’s exact test. The prevalence of treatment emergent adverse events will be described using summary statistics. For gene expression analysis, we will designate subjects diagnosed with a *Candida* bloodstream infection as case patients and those who remained uninfected and had negative B-D-glucan testing as controls. Decision tree analysis will be used to develop predictive signatures for candidemia versus no infection.

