**Preemptive Antifungal Therapy Based on Fungal Biomarkers**

β-D-glucan (BDG) is a cell wall constituent found in many pathogenic fungi including *Aspergillus* and *Candida* as well as *Fusarium*, *Trichosporon*, *Saccharomyces,* and *Acremonium*. Assays that are capable of detecting BDG in the serum of patients with IFI due to these organisms have been developed commercially. The β-D-glucan test (Fungitell^™^; Associates of Cape Cod, Falmouth, MA) is FDA approved as an adjunct to the diagnosis of deep-seated mycoses and fungemia. BDG analysis performed on serial serum samples obtained from 283 patients with acute myeloid leukemia or myelodysplastic syndrome who were receiving antifungal prophylaxis revealed that the test became positive a median of 10 days before the clinical diagnosis of IFI in 100% of patients(13). Absence of a positive test result had a 100% negative predictive value and a single positive test result had a specificity of 90%.

Primary prevention strategies that incorporate serial measurement of fungal biomarkers with initiation of antifungal therapy in response to a positive test represent an exciting new approach to IC management. Early initiation of appropriate antifungal therapy has been shown to improve clinical outcomes, but to date, the BDG assay has only been validated for patients with hematological malignancies and/or following transplantation. The performance of the test in the ICU setting has not been established. Poor specimen handling, hemodialysis using certain cellulose membranes, exposure to gauze products, some antibiotics, and recent receipt of albumin or immunoglobulin products may cause false positive test results in some patients(14-18). Since many of these potential sources of BDG cross-reactivity are present in the ICU population (**Table 2**), further investigation of the assay is warranted in this setting.

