**STUDY POPULATION**

**Inclusion Criteria**

Patients must meet all of the following criteria to be eligible for enrollment:

- Age ≥18 years
- Admission to the SICU or MICU for ≥ 72 hours and expected to stay and additional 48 hours
- IV access for administration of study drug
- Subject (or subject’s legal representative) able to give written informed consent

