**FOLLOW-UP (SICU DISCHARGE)**

All study subjects will be followed until SICU discharge or for as long as they are receiving study drug, whichever is longer.

- Assess whether patient has evidence IFI or meets EORTC/MSG criteria for a new proven or probable IFI at SICU discharge.
- Assess mortality at SICU and hospital discharge. Cause of death and date of death will be documented.
- Oral wash or ETS for semi-quantitative fungal culture with susceptibility testing will again be obtained at SICU discharge.

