**DESCRIPTION OF STUDY END POINTS**

**Primary Endpoints**

1. Feasibility of preemptive monitoring strategy.
2. β-D-glucan test performance in the stand care (empiric therapy) group.
3. Safety and tolerability of preemptive anidulafungin.

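### IFI ascertainment stops at SICU discharge, so BDG-positive patients diagnosed later count as false positives in the primary test-performance endpoint

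*Protocol*

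**What the plan says.** The second primary endpoint is "β-D-glucan test performance in the stand care (empiric therapy) group". Under Statistical Analyses, "β-D-glucan test characteristics, using data collected from standard care group, will be described using sensitivity, specificity, positive and negative predictive values", with proven and probable IFI by the EORTC/MSG criteria as the comparison standard.

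Three places set how long IFI is looked for:

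- Schedule of procedures, All Subjects: IFI assessments are weekly, for the duration of the SICU stay.
- Follow-up (SICU Discharge): a last IFI assessment is made at SICU discharge, and "All study subjects will be followed until SICU discharge or for as long as they are receiving study drug, whichever is longer". Standard care patients receive no study drug, so their follow-up ends at SICU discharge. Beyond that, this section asks only for mortality at hospital discharge, with cause and date of death.
- Statistical Analyses, Efficacy End-Points: "The study period is defined as the time the patient was cared for in the SICU".

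The introduction reports, from a leukemia/myelodysplasia cohort on antifungal prophylaxis, that "the test became positive a median of 10 days before the clinical diagnosis of IFI". The first hypothesis is that surveillance identifies infected patients "before clinical signs or symptoms develop". The Inclusion Criteria ask for 72 hours already spent in the unit and an expected further 48 hours. They open with "Admission to the SICU or MICU for", whereas the study period is defined by the SICU alone.

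**The concern.** The strategy rests on the test being early, but the reference standard is read over a window that may close before an early-detected infection is diagnosed. A standard care patient who turns BDG positive, leaves the unit and is diagnosed on the ward enters the table as a false positive. The longer the test's true lead, the more often this happens. In the other direction, a BDG-negative patient diagnosed after leaving the unit enters as a true negative.

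PPV is the measure most exposed, and it bears most directly on whether treatment should start on a single positive result. A statistical analysis plan cannot repair this afterwards, because the later diagnoses would not have been collected.

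**Working it through.** **Inputs from the protocol**

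- 100 patients randomised 3:1, giving 75 and 25 (Sample Size).
- 25% expected to turn BDG positive, 19 expected to receive anidulafungin (Sample Size).
- 81% of patients with IC positive at the 60 pg/ml cut-off (Active surveillance/preemptive therapy group).
- Median lead of 10 days (introduction); 48 further expected hours at entry (Inclusion Criteria).

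**Assumptions not in the protocol**

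- An IFI rate. None is stated for this population. The only nearby figure is the 10% at which experts have advocated prophylaxis (Epidemiology), which is a threshold and not an expected rate. I use 10% for illustration and show 5% and 15%.
- The fraction f of IFI cases diagnosed after SICU discharge: 0, 25% or 50%, taken to be the same for BDG-positive and BDG-negative cases.
- The 81%, which is quoted for IC, is applied to all IFI.

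**Step 1. The plan's own figures reproduce.** 100 × 3/4 = 75. 75 × 0.25 = 18.75, which rounds to 19. In standard care, 25 × 0.25 = 6.25 positives are expected.

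**Step 2. Table with complete ascertainment, 10% IFI.**

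- Cases: 25 × 0.10 = 2.5
- True positives: 0.81 × 2.5 = 2.03
- False positives: 6.25 − 2.03 = 4.22
- False negatives: 2.5 − 2.03 = 0.47
- True negatives: 22.5 − 4.22 = 18.28
- PPV = 2.03/6.25 = 32%; specificity = 18.28/22.5 = 81%; NPV = 18.28/18.75 = 97.5%

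**Step 3. Move a fraction f of cases past SICU discharge.** True positives become (1 − f) × TP, and f × TP is added to the false positives. False negatives become (1 − f) × FN, and f × FN is added to the true negatives. Observed PPV is therefore (1 − f) times true PPV.

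| Assumed IFI rate | f | PPV | Specificity | NPV |
|---|---|---|---|---|
| 5% | 0 | 16.2% | 77.9% | 98.7% |
| 5% | 25% | 12.2% | 77.2% | 99.0% |
| 5% | 50% | 8.1% | 76.4% | 99.4% |
| 10% | 0 | 32.4% | 81.2% | 97.5% |
| 10% | 25% | 24.3% | 79.5% | 98.1% |
| 10% | 50% | 16.2% | 77.9% | 98.7% |
| 15% | 0 | 48.6% | 84.9% | 96.2% |
| 15% | 25% | 36.5% | 82.1% | 97.1% |
| 15% | 50% | 24.3% | 79.5% | 98.1% |

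Sensitivity stays at 81% here only because f is the same for both kinds of case. If BDG-positive cases surface late more often than BDG-negative ones, observed sensitivity falls as well.

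**Step 4. Number of cases behind sensitivity.** Expected cases = 25 × rate. The chance of no case at all is (1 − rate)^25.

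| Assumed IFI rate | 2% | 5% | 10% | 15% | 20% |
|---|---|---|---|---|---|
| Expected cases | 0.5 | 1.25 | 2.5 | 3.75 | 5 |
| P(no case) | 60% | 28% | 7% | 1.7% | 0.4% |

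Exact (Clopper-Pearson) 95% intervals for sensitivity: 3 of 3 detected gives 29% to 100%; 4 of 5 gives 28% to 99%.

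**The case against.** **Against the point itself**

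- The sentence defining the study period sits under Efficacy End-Points, and the BDG paragraph sets no window. This is correct. The limit reaches accuracy through the schedule: IFI is assessed during the SICU stay and at SICU discharge, and no later assessment exists to draw on.
- The 10-day lead comes from leukemia/myelodysplasia patients, and the protocol says that performance in the ICU has not been established. The 48 hours is an expectation at entry, not a typical stay. Both facts leave the size open. Neither changes the direction.
- The shift is within sampling error. At 10% IFI the standard error of specificity is about √(0.81 × 0.19/22.5) = 8 points, and of PPV about √(0.32 × 0.68/6.25) = 19 points. This stands for a single trial of this size. But it is a bias in a known direction that can be removed cheaply.
- The small sample is disclosed. The Sample Size section ties it to accrual and cost, calls the aim a preliminary feasibility evaluation and claims no precision for accuracy. The sample size is therefore not faulted here.

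**Stronger readings that the documents do not support**

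- A reader might infer that the BDG-negative patients of the 75-patient arm could be pooled to sharpen NPV. Under Discontinuation from Study, patients in that arm started on systemic antifungals without a positive BDG or a new proven or probable IFI are discontinued and then followed only for mortality. Their IFI outcome would be missing precisely where infection was suspected. Only that arm may have off-schedule tests, and its clinicians see the results. The protocol restricts accuracy to standard care deliberately, to avoid such bias.
- A reader might infer that longer follow-up of treated preemptive patients distorts this endpoint. It cannot, because the endpoint is read in standard care only.
- A reader might turn the 10-day median into a precise loss of PPV, or state two or three cases as fact. The first needs a lead-time distribution and remaining SICU stays that the protocol does not give. The second needs the assumed 10% rate.

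**Conclusion.** The point holds. For standard care patients, ascertainment of the reference standard ends at SICU discharge, although the protocol's own rationale is that positivity precedes diagnosis by days. Followed as written, the plan understates PPV, slightly understates specificity and overstates NPV for a primary endpoint.

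The size is unknown. Under the 10% illustration, PPV loses about 8 or 16 points and specificity about 2 or 3 points, if a quarter or a half of cases surface after discharge. These figures rest on an assumed IFI rate, an assumed late fraction common to both test results, and the protocol's 81% and 25%.

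Separately, sensitivity will rest on about 0.5 to 5 expected cases for assumed IFI rates of 2% to 20%. Longer follow-up removes misclassification but does not cure that. Admitting MICU patients while defining the study period by the SICU is a wording conflict that leaves a MICU patient's window undefined.

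**What to change.** 1. Extend IFI ascertainment in both arms to hospital discharge by chart abstraction, at the time when mortality is already collected. Use this as the reference standard for BDG accuracy and keep the SICU-only result as supportive.
2. State the ascertainment window in the β-D-glucan Test Characteristics paragraph itself.
3. Keep accuracy in the standard care arm only, without pooling.
4. Describe sensitivity as resting on a handful of cases, with the assumed IFI rates shown.
5. Reconcile the SICU-or-MICU inclusion criterion with the SICU-only definition of the study period.

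The cost is one extra chart abstraction per patient, plus wording; the protocol already requires patients to allow access to their medical records. The downside is that some infections acquired after the last BDG sample will count as misses. Reporting the time from last sample to diagnosis for each case lets the reader separate these from true test failures.

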**Stratification and Randomization**

Patients who meet inclusion/exclusion criteria and provide written informed consent will be stratified into 2 groups based on APACHE II score. Group 1 will have APACHE II scores ≤ 20 and group 2 > 20. Subjects within each APACHE II group will then be assigned to either active surveillance with preemptive anidulafungin based on a positive BDG test or standard care using a 3:1 randomization schedule (approximately 75 subjects in the preemptive group and 25 in the standard care group). The study coordinator will assign each patient to the next available randomization number which will be generated using randomization software. Patient study identification (ID) numbers will also be assigned sequentially starting with Patient No. 1. Dropouts will not be replaced.

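### SICU stay and febrile days are ranked with deaths counted as short stays, by a test that ignores the APACHE II strata; the first can favour the arm with more deaths, the second costs some power

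*Protocol*

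**What the plan says.** Under Stratification and Randomization, patients "will be stratified into 2 groups based on APACHE II score": "Group 1 will have APACHE II scores ≤ 20 and group 2 > 20". Allocation is 3:1 within each stratum.

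Under Statistical Analyses, Efficacy End-Points, "The median ICU stay and number of febrile days while in the ICU will be compared using the Kruskal-Wallis test". For infection outcomes, "The proportions of patients developing IFI, and IC specifically, in each group will be compared using" Fisher's exact test. Mortality is to be summarised by group, with no test named. The Safety section names a chi-square test for adverse events. None of these tests carries the APACHE II strata, and no other section brings them into an analysis.

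The same section limits the study period to time in the SICU. The Censoring section makes withdrawal of consent the only reason for censoring, and Data Analysis places all primary and secondary analyses on an intention-to-treat basis. Duration of SICU stay and number of febrile days are items 2 and 3 of the Secondary Endpoints. Under Sample Size, "This study will not be powered to show a difference in the efficacy of preemptive management versus standard care".

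**The concern.** Days in the SICU end either by discharge or by death. Taken together, the Protocol's rules keep a patient who dies in the unit in the analysis, uncensored, with the days accrued up to death. A rank test on those raw days puts an early death beside an early recovery. Febrile days behave the same way, because death stops the count.

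If the arms have the same mortality, this does no systematic harm. If mortality differs, and deaths tend to come before survivors' discharges, the arm with more deaths shows shorter stay and fewer febrile days. A strategy that prevents deaths would then look worse on both endpoints. That is an error of direction, so low power does not excuse it.

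The unused strata are a lesser matter. Stratified allocation balances a prognostic factor, but an unstratified test leaves the between-stratum variation in its error term. Its true error rate then falls below 5% and it loses power.

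**Working it through.** **The plan's own figures.** 100 × 3/4 = 75 and 100 × 1/4 = 25, as stated ("75 will be assigned to active surveillance and 25 to standard care"). The expected number treated is 75 × 0.25 = 18.75, rounded to 19, as stated. The Protocol gives no mortality, length of stay, stratum sizes or power for the arm comparisons. Everything below assumes those values, with 75 against 25 patients and two-sided 5%, so 2.5% in each direction.

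**1. Deaths and SICU stay, in closed form.** With two groups, Kruskal-Wallis is the two-sided rank-sum test.
- Assume lognormal stay with log-SD 0.7, median 10 days for survivors and 5 for deaths, identical in both arms given vital status.
- A death's stay is shorter than a survivor's with probability Φ(ln 2 / (0.7 × √2)) = Φ(0.700) = 0.758.
- With mortality p1 (preemptive) and p0 (control), the chance that a preemptive stay exceeds a control stay is 0.5 + (0.758 − 0.5) × (p0 − p1).
- The null standard deviation of that statistic is √(101 / (12 × 75 × 25)) = 0.067.

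| Mortality, preemptive vs control | Shift / SD | Significant in the lower-mortality arm's disfavour: formula | Simulation |
|---|---|---|---|
| 15% vs 30% | 0.0387 / 0.067 = 0.58 | 1 − Φ(1.96 − 0.58) ≈ 8% | 8% |
| 40% vs 20% | 0.0516 / 0.067 = 0.77 | 1 − Φ(1.19) ≈ 12% | 11% |
| 40% vs 10% | 0.0774 / 0.067 = 1.16 | 1 − Φ(0.80) ≈ 21% | 21% |

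In the first row the preemptive median is 0.8 days longer on average and longer in 68% of trials. The shift disappears if deaths and discharges have the same timing, and it reverses if deaths come later.

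**2. A second model.** Stay is lognormal with median 8 days and log-SD 0.7. The high stratum stays 1.5 times as long, death cuts the stay at a uniform fraction, and there are 4,000 runs per scenario.
- Control vs preemptive mortality of 20% vs 30%, 20% vs 40% and 10% vs 40%: the preemptive arm tests significantly shorter in 5.6%, 10.3% and 19.1% of trials.
- With deaths given the worst rank, significance in that arm's favour falls to 0.3%, 0% and 0%.
- At 20% in both arms, the raw test favours the preemptive arm in 1.6%, so there is no bias when mortality is equal.
- In large samples without the stratum effect, median stay falls from 8.0 days with no deaths to 7.1 at 20% mortality and 6.2 at 40%. If 30% of days are febrile, mean febrile days fall from 3.1 to 2.8 and 2.5.

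**3. Unused strata, SICU stay, no deaths.** Same stay model, strata of about equal size, permuted blocks of 4, 4,000 runs. Power is for a 35% shorter stay.

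| Stay ratio, high/low stratum | Size: Kruskal-Wallis | Size: van Elteren | Power: Kruskal-Wallis | Power: van Elteren |
|---|---|---|---|---|
| 1 | 5.1% | 5.1% | 72% | 72% |
| 1.5 | 4.0% | 5.1% | 69% | 71% |
| 2 | 2.9% | 5.2% | 63% | 72% |
| 3 | 1.1% | 4.7% | 51% | 73% |

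The power loss depends on how the 25 controls fall. With 12 controls in the short-stay stratum and 13 in the long-stay stratum, Kruskal-Wallis power falls from about 73% to about 69% at 2-fold and 58% at 3-fold. That split is favourable, because 13/25 = 52% of controls but 37/75 = 49% of preemptive patients are long-stayers. The opposite split loses more. Size is about 3% and 1% either way.

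**4. Unused strata, IFI and IC.** Assume stratum rates of 5% and 15%, averaging 10%, so about 25 × 0.10 = 2.5 control events. At an odds ratio of 0.33 and 20,000 runs, power is 22.0% for Fisher and 22.0% for its exact stratified counterpart. It is 27.2% for Mantel-Haenszel, unstratified or stratified. The gap is exact against asymptotic testing; the strata add nothing.

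**The case against.** The strongest case against is that little hangs on this. The endpoints are secondary, the trial is a feasibility study that disclaims power for efficacy, and mortality is reported by arm, so a careful reader could see what lies behind a shorter stay. This stands and keeps the priority modest.

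The mortality contrasts are also large for the mechanism. Only about 19 of 75 are expected to receive anidulafungin. A fall from 30% to 15% means 0.15 × 75 ≈ 11 deaths averted, and a rise from 20% to 40% means 0.20 × 75 = 15 extra deaths. If the drug is the route, those fall among about 19 patients. So the figures illustrate the bias; they do not predict its size. Its direction also depends on deaths coming earlier than discharges, which the Protocol does not establish. The exclusion of moribund patients removes only the earliest deaths.

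A third argument is that handling of death and stratified analyses are commonly left to a statistical analysis plan. That would hold if the Protocol were silent. Here it names the tests and fixes an exclusive censoring rule, and those rules together produce the problem.

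A reader might infer that unstratified testing inflates false positives or undermines the IFI and IC comparisons. It does not: the tests become conservative, and for events this sparse the strata make no visible difference, so Fisher's test is defensible there. A reader might also apply Fisher's shortfall to mortality, but no test is named for mortality. Finally, the Protocol never says that a shorter stay is better. That is only the natural reading of such a comparison.

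**Conclusion.** The point holds for SICU stay and febrile days. As written, the comparison favours the arm with more deaths whenever mortality differs and deaths precede discharges. Under the assumed inputs, a wrong-direction significant result occurs in roughly 6% to 21% of trials against a nominal 2.5%. The range follows the assumed mortality gap, from 10 to 30 percentage points.

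Ignoring APACHE II is the smaller part. It is immaterial when stay is similar across strata. At assumed 2- to 3-fold ratios, size falls to about 3% and 1%, and power from about 72% or 73% to 63%–69% and 51%–58% for the allocations tabulated or stated above. There is no material loss for IFI or IC.

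The documents do not support reading this as a threat to the trial's primary conclusions, which concern feasibility, test performance and safety. It is a modest-priority correction to two secondary comparisons.

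**What to change.** In Statistical Analyses, replace the Kruskal-Wallis sentence. Compare SICU stay and febrile days between arms with a van Elteren test stratified by APACHE II (20 or below, above 20), giving death in the SICU the worst rank. For stay, an alternative is time to SICU discharge alive with death as a competing event. Show the raw medians and mortality by arm beside the result.

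Optionally, use a Cochran-Mantel-Haenszel test or a stratified risk difference for IFI, IC and mortality. State that the gain for sparse IFI or IC is negligible, and that this would be the first test named for mortality.

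Two tempting alternatives should be avoided. SICU-free days to day 28 need day-28 status, but under Follow-up observation ends at SICU discharge or the end of study drug, with mortality only to hospital discharge. Febrile days per SICU day alive does not cure the bias, because an early afebrile death still scores zero, the best value.

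The recommended change costs wording only. APACHE II is scored before randomisation, deaths and their dates are already recorded, and the methods are standard in SAS. The small downside is that a worst-rank result mixes mortality with duration, so it needs a sentence of explanation.
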